### Statistical analysis

2.7

Data management uses EXCEL software to build a database, double entry, check for outstanding values, and lock. Statistical analysis will be performed using SPSS 25.0 software for statistical analysis. The normality of the measurement data is tested. The data obeying the normal distribution is Student's *t* test, which is expressed by mean ± standard deviation. The data not obeying the normal distribution is rank sum test. And marginal homogeneity test; count data are expressed by rate and composition ratio, and comparison is performed by chi-square test; repeated measurement data are expressed by mean ± standard deviation, intra-group comparison is performed by analysis of variance of repeated measurement data, and inter-group comparison is by multivariate analysis of variance (MANOVA). *P* ≤ .05 indicates that the difference is statistically significant.

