### Interventions

2.3

The participants included in the observation will be self-controlled, and each patient randomly selected 3 different scar treatment areas at the same site as observation specimens.

Control group: Take the untreated pathological scars of the participants as blank control. This group will not give any intervention.

Intervention group: Among the two pathological scars, group A will be treated with conventional external medicine of western medicine, and group B will be treated with oral TCM decoction combined with conventional external medicine of western medicine. The main components of the TCM prescription are: *Baizhi, Jiazhu, Leiwan, Maidong, Yuanhu, Taoren, Honghua*, and *Jingjie*. Specific treatment method: clean the scar area, apply gel to the affected area, every 3 times. TCM decoction is taken orally after meals, 3 times a day. The total application time will be 8 weeks. At the same time, closely monitor the change of the condition in order to control the deterioration of the condition in time (Fig. 2).

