### Outcome measures

2.4

The assessment of scar area, color, hardness, thickness, itching, and pain was recorded for 8 weeks of treatment. Assess fatigue marks once a week and save case photos.

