#### Primary outcome measures

2.4.1

We will use the international scar evaluation method—“*Vancouver Scar Evaluation Scale*” as the main standard for evaluating the efficacy.

1.Color: 3 points for bright red, 2 points for light red, and disappear after pressing, 1 point for non-red or some gray, 0 points for normal skin color;2.Height of scar marks: 3 points above 9 mm, 5 mm < 2 points for height ≤9 mm, 1 point for 1 to 5 mm, 0 points for flat or slightly depressed;3.Hardness: 3 points for hard as cartilage, 2 points for hardness like rubber, 1 point for softness, normal for softness skin score: 0 points;4.Itching: 3 points for severe or persistent itching, 2 points for frequent and tolerable itching, sometimes 1 point for itching, and 0 points for no itching;5.Pain: very intense 3 points for the “hyperalgesia,” 2 points for moderate-intensity allergic pain, sometimes 1 point for pain, and 0 points for no pain;6.tightness: 3 points for strong tightness, not too tight strong and tolerable score 2 points, slight tightness score, no tightness score 0 points.

Efficacy index = (total score before treatment − total score after treatment)/total score before treatment × 100%.

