### Sample size calculation

2.5

The sample size for this trial is based on an expected mean difference between groups of 11 points of the Constant–Murley questionnaire, which is the minimum clinically important difference. To detect this difference between both treatments, with a value of *a* = 0.05 (probability of committing a type I error) and a statistical power of 95%, a minimum of 49 patients per group is needed. This minimal sample size estimate has been increased by 20% after considering the potential dropouts, finally including 60 patients for each group. Accordingly, the proposed experimental hypothesis is that there will be a difference of at least 11 points in the Constant–Murley questionnaire in the intervention group versus the control group. The sample size was determined using the Stata SE software, version 15.

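### A normality test on the outcome data chooses between a t test and a rank sum test, so the hypothesis behind a single-value efficacy comparison is not fixed in advance

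*Protocol article*

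**What the plan says.** Section 2.7 (Statistical analysis) begins its rule with a pre-test: "The normality of the measurement data is tested". Two branches follow: "The data obeying the normal distribution is Student's" t test, and "The data not obeying the normal distribution is rank sum test". No variable is exempted, and no test is named as primary. The same section gives repeated measurements a separate route without a normality gate: repeated-measures ANOVA within groups, while "inter-group comparison is by multivariate analysis of variance (MANOVA").

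Section 2.4.1 scores six items from 0 to 3 and defines "Efficacy index = (total score before treatment − total score after treatment)/total score before treatment × 100"%. That is one value per scar, so it falls under the gated rule. Section 2.4 adds weekly assessments ("Assess fatigue marks once a week and save case photos"). Section 2.3 makes patients their own controls: "each patient randomly selected 3 different scar treatment areas at the same site as observation specimens", one left untreated and two treated differently.

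Section 2.5 bases the sample size on a mean difference between groups, with alpha "0.05 (probability of committing a type I error"), sidedness not stated. It gives 49 per group, raised to 60.

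**The concern.** The t test concerns a difference in means. The rank sum test concerns whether values in one condition tend to exceed those in the other. The two agree for a pure shift but can part when the shapes of response differ. If the data choose the test, they also choose the hypothesis, and a report could contain a mean difference for one contrast and a statement about ordering for another. When the rank branch is taken, the mean hypothesis of Section 2.5 is not the one tested.

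A bounded integer total makes this a practical matter. Its distribution becomes skewed as scores move towards zero, which is where successful treatment would take them. At about 50–60 scars per condition on such a scale, a comparison of means does not need normal data, so the pre-test protects little.

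**Working it through.** The plan gives no figure for this point. The 49 per group cannot be reproduced because no standard deviation is stated, and nothing below depends on it.

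**Inputs from the protocol article.** Total score: 6 items × 3 points = 18 at most (2.4.1). Three conditions, hence 3 pairwise contrasts (2.3). 60 per group, with 49 as the minimum (2.5). Significance at P ≤ .05 (2.7).

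**Assumptions.** The pre-test is Shapiro-Wilk at 0.05 in each condition; the t test is used only if both conditions pass. Tests are two-sided. Item scores come from correlated latent normals (correlation 0.35–0.4), rounded and clipped to 0–3.

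**Step 1: exactly normal data, independent samples.** Both of two samples pass with probability 0.95² = 0.90. The three contrasts receive a mixture of tests when exactly one of three samples fails: 3 × 0.05 × 0.95² = 0.135. Simulation gave about 13%.

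**Step 2: the 0–18 total at 60 per condition.**
- Mean about 9: both conditions pass in about 75% of trials (75% to 78% across runs).
- Mean about 5.4: both pass in about 11% (10% to 11%).

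Mixture of t and rank sum tests over the three contrasts, in simulation (independent samples, latent correlation 0.4):

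| Per condition | No difference | Conditions differ |
|---|---|---|
| 49 | 25% | 39% |
| 60 | 28% | 46% |
| 120 | 44% | 22% |

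Check at 60 with no difference: both pass in about 77%, so one sample passes with probability √0.77 = 0.8775, and 3 × 0.77 × (1 − 0.8775) = 0.283, in line with 28%. The row for 120 is shown because the article can also be read as 120 patients who each contribute to all three conditions.

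**Step 3: type I error with identical distributions.** The two-stage rule rejects in about 4% to 6% of trials.

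**Step 4: equal means, different shapes.** One condition changes by N(3, 1.5²). The other is a mixture with the same mean:
- strong: 0.3 × 7 + 0.7 × 1.286 = 3.0
- milder: 0.3 × 5 + 0.7 × 2.143 = 3.0, or 0.5 × 5 + 0.5 × 1 = 3.0

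| Scenario, 60 per condition unless stated | t test | Gated rule |
|---|---|---|
| Strong responders, unpaired | about 5% | about 20–22% |
| Normal against shifted exponential, unpaired | 5.0% | 11.5% |
| Milder responders, unpaired | – | about 4–6% (lowest run 3.4%) |
| Strong responders, paired | 4.6–5.4% | 5.1–6.0% |
| Strong responders, paired, 120 patients | 5.5% | 6.8% |

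The paired rows at 60 use within-patient correlations of 0, 0.3 and 0.5.

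**Step 5: what the gate contributes.** In the strong-responder unpaired scenario both samples pass in only about 0.2% of trials, so the gated rule is in effect the rank sum test (20.6% for both in one run). The excess over 5% reflects the different null hypothesis of the rank test, not the act of pre-testing.

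**The case against.** The rule is written down in advance and Section 2.6 blinds the statistician to group, so the choice of test is algorithmic and not discretionary. That is so, and it removes any suggestion of picking the favourable test. It does not settle which hypothesis is tested.

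A reader might infer three stronger things that the documents do not support.

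- *The rule inflates false positives generally, to about 20%.* That figure needs unpaired tests and one extreme responder pattern. A pre-specified rank sum test would give the same figure. With paired tests, which the self-controlled design calls for, it falls to about 5–7%. The article gives no response distribution or responder fraction by which to prefer that scenario. Section 2.7 does name the rank sum test and says nothing of pairing, but that is a separate defect.
- *The test will switch from visit to visit.* Weekly scores plausibly go to the ungated ANOVA/MANOVA route. Switching between visits arises only if visits are compared singly, which the text leaves open.
- *Single 0–3 items will always fail the normality test, so the primary analysis is affected.* Efficacy is defined on the total, and consistent failure would give items one consistent test.

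The name and level of the normality test are details that an analysis plan may supply, and their absence is not criticised here.

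**Conclusion.** The point holds as a matter of an unfixed hypothesis. Section 2.7 states a data-dependent choice between two tests with different null hypotheses, applies it without exemption to single-value efficacy measures, and does not say whether that route or ANOVA/MANOVA decides efficacy. Section 2.5 frames the question as one about means; it does so for a questionnaire other than the scar scale, which is a separate matter.

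The instability is real under the assumed score model: the chance that both conditions pass falls from about 75% to about 11% between means of 9 and 5.4. The effect on error rates is modest or conditional: near 5% with identical distributions, and about 4% to 22% unpaired or 5–7% paired when means are equal but shapes differ. The unpaired range is for 60 per condition; its upper end would rise with more patients. All of these rates depend on an assumed score model, assumed responder patterns and an assumed pre-test. The plan should be changed on this point, but the gate alone would not invalidate the trial.

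**What to change.** In Section 2.7, delete the normality gate for the primary outcome and name one deciding analysis: the mean between-condition difference in the primary scar-score measure at week 8, with 95% CI, from a within-patient analysis (paired, or a mixed model) suited to the self-controlled design. Removing the gate does not require replacing the efficacy index; the sponsor should state which scar-score measure is primary. Name the corresponding rank test as a sensitivity analysis, signed rank if the analysis is paired, and state the role of the repeated-measures ANOVA and MANOVA.

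The cost is one or two sentences. No new data are needed, and Section 2.9 says that recruitment has not started. If scores are heavily skewed, the mean-based analysis may have slightly less power than a rank test.

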#### Inclusion criteria

2.2.2

This study will be conducted in China. Patients will be recruited from Plastic surgery departments of the Second Affiliated Hospital of Shaanxi University of Chinese Medicine. We will enroll participants based on the following inclusion criteria:

1.It meets the diagnostic criteria for pathological scars;2.There are at least 3 pathological healing scars throughout the body.3.Female patients of 16 ≤ age ≤ 40 years old;4.The time for the formation of fatigue marks exceeds 3 months;5.Those who have voluntarily signed the informed consent.

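### The three conditions are scars on the same patient, but section 2.7 names rank sum, chi-square and between-group MANOVA, which as named assume independent groups

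*Protocol article*

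**What the plan says.** Protocol article, section 2.3 (Interventions): "The participants included in the observation will be self-controlled, and each patient randomly selected 3 different scar treatment areas". The control arm is defined by the instruction "Take the untreated pathological scars of the participants as blank control". The treated arms are the other two scars: "Among the two pathological scars, group A will be treated with conventional external medicine of western medicine", while group B adds an oral decoction to the same topical treatment. Section 2.2.2 (Inclusion criteria) fits this: "There are at least 3 pathological healing scars throughout the body". The abstract also uses the enrolled patients' own untreated scars as the control.

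Section 2.7 (Statistical analysis) lists the tests:

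- Student's t test for normal data, with pairing not stated.
- For other measurement data, "The data not obeying the normal distribution is rank sum test".
- A marginal homogeneity test, in a sentence fragment tied to no outcome.
- For categories, "count data are expressed by rate and composition ratio, and comparison is performed by chi-square test".
- For the repeated measurements, repeated-measures ANOVA within a group, whereas "inter-group comparison is by multivariate analysis of variance (MANOVA").

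Sections 2.5 and 2.6 describe something else: 60 patients in each of two groups, with patients randomized.

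**The concern.** Under section 2.3, the untreated, A and B scars share a patient, a skin type and a body site, so their scores are likely to move together. The rank sum test, the chi-square test and a between-group MANOVA compute the error of a difference as if the scars came from different people. Section 2.7 itself separates a repeated-measures method for within-group change from MANOVA for group differences, which puts treatment group on the independent side. No matched, clustered or mixed method is attached to the total score, the weekly series or the efficacy categories.

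This is not a detail left to a later document. The article names the methods, and they do not fit the design it describes. At stake are the validity of the p-values for the main comparison and the precision that a self-controlled design is meant to buy.

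**Working it through.** **The plan's own figure.** Section 2.5 gives a difference of 11 points on the Constant–Murley questionnaire, alpha 0.05, power 95% and 49 patients per group. No SD is stated, so 49 cannot be derived from the stated inputs. The two-independent-group formula is n = 2·SD²·(1.960 + 1.645)²/11². With SD 15 it gives 2 × 225 × 12.996/121 = 48.3, rounded up to 49. The planned 95% power is therefore consistent with an unpaired two-group calculation, two-sided, with SD about 15.

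**Effect of ignoring the pairing.** Let ρ be the correlation between two scars of one patient. The documents give no value; 0.3, 0.5 and 0.7 are assumptions.

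- The true variance of the difference in means is (1 − ρ) times what an unpaired test assumes.
- True type I error = 2·[1 − Φ(1.960/√(1 − ρ))].
- Ratio of unpaired to paired interval width = 1/√(1 − ρ).

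| ρ | √(1 − ρ) | 1.960/√(1 − ρ) | true type I error | width ratio |
|---|---|---|---|---|
| 0.3 | 0.837 | 2.343 | 1.9% | 1.20 |
| 0.5 | 0.707 | 2.772 | 0.6% | 1.41 |
| 0.7 | 0.548 | 3.578 | 0.03% | 1.83 |

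**Simulation check.** Two scars per patient, 60 patients, no true difference, nominal 5%; 8,000 runs (4,000 for MANOVA). Chi-square used a split at the median. MANOVA used eight weekly values with an assumed correlation of 0.6 between weeks.

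| test | ρ = 0.3 | ρ = 0.5 | ρ = 0.7 |
|---|---|---|---|
| unpaired t | 0.021 | 0.006 | 0.001 |
| rank sum | 0.022 | 0.008 | 0.001 |
| chi-square | 0.034 | 0.018 | 0.006 |
| two-group MANOVA | 0.004 | 0.001 | 0.000 |

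Paired counterparts (paired t, McNemar, paired Hotelling) stayed between 0.043 and 0.057. At ρ = 0 the two approaches agree.

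**Efficiency forgone.** For a difference of 0.3 SD at ρ = 0.5, simulated power was 0.32 unpaired against 0.62 paired with 60 patients, and 0.70 against 0.91 with 120. Equivalently, with SD 15 and a difference of 11, the number of pairs for 95% power is SD²·2(1 − ρ)·(1.960 + 1.645)²/11². This gives 34, 25 and 15 pairs for ρ = 0.3, 0.5 and 0.7, against 49 at ρ = 0.

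**Missed weeks (secondary).** Section 2.4 has weekly assessment over 8 weeks. If MANOVA takes all eight values, only complete series enter. With a chance m of missing each visit, independently, the complete share is (1 − m)^8: 92% at m = 1%, 85% at 2%, 66% at 5% and 43% at 10%. These rates are assumptions; the documents give none.

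**The case against.** The strongest reply is that the fault lies in the design description. Sections 2.5 and 2.6 set out two parallel groups of patients, and for one value per patient independent-group tests would be acceptable. That stands as a reason to reconcile those sections with 2.3 first. It does not clear section 2.7, because under 2.3 the untreated control is the patient's own scar.

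A second reply is that the test names are loose: the t test may be meant as paired, and the marginal homogeneity test is a related-samples method. The t test is indeed ambiguous, and this point does not rest on it. The marginal homogeneity test suits paired categories, but the text does not say what it serves, and categories are separately assigned to chi-square.

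Three stronger readings are tempting, and the documents do not support them.

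- *Power falls below the planned 95%.* That would require the 95% to refer to a paired test, but section 2.5 sizes two independent groups. On that basis, an unpaired test applied to paired scars has power Φ(1.645/√(1 − ρ)) = Φ(1.966), Φ(2.326), Φ(3.003), or about 97.5%, 99.0% and 99.9%. Efficiency is forgone; the planned power is not lost.
- *False positives are inflated because several scars per patient are pooled to compare patient groups.* No section states such an analysis.
- *Every listed test discards incomplete weekly series.* Only standard MANOVA does. Chi-square and rank sum use one value per scar, and section 2.7 does not say that all eight weeks enter the MANOVA. A missing-data rule may stand in a document not shown.

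**Conclusion.** The concern holds in a limited form. Read with the design in section 2.3, the rank sum, chi-square and between-group MANOVA named in section 2.7 give wrong p-values whenever scars within a patient correlate. With positive correlation the error is conservative. For the unpaired t test, true type I error is about 2%, 0.6% and below 0.1% at assumed correlations of 0.3, 0.5 and 0.7, and the other tests err in the same direction. Intervals, which section 2.7 does not mention, would be 20%, 41% and 83% too wide if computed unpaired. The cost is a weaker analysis than the design allows, not spurious significance.

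The size rests on the assumed correlation, and there is no error if it is zero. The loss of incomplete series is secondary and conditional on how MANOVA is run.

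**What to change.** First reconcile sections 2.3, 2.5 and 2.6 on whether scars or patients are the allocated unit. No analysis model can settle that, nor whether an orally taken decoction can be assigned to a single scar.

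If the within-patient design stands, replace the independent-group tests in section 2.7 as follows.

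- **Weekly total score:** a linear mixed model with a random patient effect, scar within patient and repeated weeks. Fixed effects are condition (three levels: untreated, A, B), week, condition-by-week and the baseline score. Report the contrasts between conditions at week 8 with 95% confidence intervals. Use one three-level factor, not separate topical and decoction factors with an interaction: section 2.3 has no decoction-only scar, so that interaction cannot be estimated. The model also uses scars with a missed week.
- **Efficacy categories in section 2.4.2:** matched tests for pairs of conditions (marginal homogeneity, or McNemar for a two-way split), or an ordinal model with a random patient effect. State which outcome the marginal homogeneity test serves.

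If patients are allocated to groups instead, keep patient as a random effect whenever more than one scar per patient is analysed.

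Once the design is settled, the cost is revised wording and a little more analysis work in the SPSS version already named. Section 2.9 says recruitment has not started.

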#### Efficacy evaluation

2.4.2

Refer to “*Guidelines for Clinical Research of New Chinese Medicine*.” Efficacy was evaluated by the ratio of the difference between the points before and after treatment compared to the points before treatment. Syndrome treatment efficiency = (total points before treatment total points after treatment) / total points before treatment × 100%.

1.Clinical control: clinical symptoms and signs disappeared or basically disappeared, and syndrome scores were reduced by ≥95%;2.Significant effect: clinical symptoms and signs were significantly improved, and syndrome scores were reduced by 70%;3.The signs and symptoms have improved, and the syndrome scores have decreased by ≥30%;4.Ineffective: the clinical symptoms and signs have not improved significantly, and the syndrome scores have decreased by <30%.

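### Three conditions share one blanket P ≤ .05 rule, and no contrast or time point on the primary scar score is named as decisive; reading any of three pairwise tests as efficacy gives about 12% false-positive risk, not 5%

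*Protocol article*

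**What the plan says.** - **Threshold (2.7 Statistical analysis).** The section lists Student's t or rank sum, marginal homogeneity, chi-square, repeated-measures ANOVA within groups and MANOVA between groups. It closes with one rule for all: "P* ≤ .05 indicates that the difference is statistically significant".
- **Conditions (2.3 Interventions).** Each patient contributes three scars. One is an untreated blank. For the other two, "group A will be treated with conventional external medicine of western medicine, and group B will be treated with oral TCM decoction combined" with the same external medicine. The label for the intervention group covers both A and B.
- **Outcomes (2.4).** The Vancouver scale is headed as primary and called the main standard (2.4.1). A four-class grade follows under its own heading (2.4.2): "Efficacy was evaluated by the ratio of the difference between the points before and after treatment compared to the points before treatment". Scoring is weekly over 8 weeks: "Assess fatigue marks once a week and save case photos".
- **Design error rate (2.5 Sample size calculation).** The calculation works "with a value of *a* = 0.05 (probability of committing a type I error) and a statistical power of 95" percent, for an "expected mean difference between groups of 11 points of the Constant–Murley questionnaire", with one hypothesis of intervention against control.
- **Allocation (2.6).** Participants are randomised to two groups.

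**The concern.** The 5% type I error in 2.5 belongs to a single comparison. Three conditions allow three pairwise comparisons, and 2.7 gives each the same threshold without saying which one answers the trial's question.

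The contrasts do not answer the same question. A versus blank concerns the external medicine alone. B versus blank concerns the combined package. B versus A is the only one that could concern the added decoction. If the choice stays open until the data are seen, a claim for combined treatment could rest on whichever contrast came out positive, and the real false-positive risk would be well above the nominal figure.

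**Working it through.** **Step 1. The plan's own figure.** Inputs from 2.5: difference 11, alpha 0.05, power 95%, 49 per group. No standard deviation is given and sidedness is not stated, so 49 cannot be reproduced forwards. Solved backwards, two-sided:

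SD = 11 × √(49/2) / (1.960 + 1.645) = 11 × 4.950 / 3.605 ≈ 15.1

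One-sided, the implied SD is 16.6. Dropout: 49 × 1.2 = 58.8, so 59; 49 / 0.8 = 61.25, so 62. The stated 60 lies between these. The calculation therefore covers one two-group comparison, on a scale other than the six-item scar score (maximum 6 × 3 = 18 points).

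**Step 2. Can the deciding comparison be recovered from the text?**

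| Section | What it implies |
|---|---|
| 2.3 | three conditions in each patient; three possible pairwise contrasts |
| 2.4.1 | Vancouver scale primary; no contrast or week named as decisive |
| 2.5 | one contrast, intervention versus control; A and B not distinguished; different instrument |
| 2.6 | two randomised groups |
| 2.7 | two-sample tests among others, all at P ≤ .05 |

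It cannot. The three contrasts are not listed either, but t and rank sum tests compare two sets at a time, so using them between three conditions means pairwise testing.

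**Step 3. Three contrasts, one outcome, one time point, no true effect.** Each test is taken as two-sided at 0.05.

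- If the tests were independent: 1 − 0.95³ = 0.143.
- They are not independent. With equal variances and equal numbers, two contrasts that share a condition have absolute correlation σ² / 2σ² = 0.5. An equal correlation between scars of the same patient cancels from this ratio.
- Simulation with that correlation: 0.122 (200,000 normal draws). A separate simulation of paired t tests in 120 patients gave 0.125.

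This is about 2.4 times 0.05 (0.122 / 0.05 = 2.44).

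**Step 4. Adding the four-class grade as a second route to a claim.** The grade was represented by a two-category response, with 60 per condition.

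| Assumed relation of response to score | Chance of at least one false positive in six tests |
|---|---|
| derived from the same score | 0.198 |
| correlation 0.8 | 0.214 |
| unrelated | 0.240 |

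A normal approximation with correlation 0.9 down to 0 between the measures gives 0.17 to 0.23. Sections 2.4.1 and 2.4.2 both use a percent reduction in points, so strong overlap is the more plausible case: about 20%.

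**Step 5. After a fix.** One named contrast at one time point returns 5%, and a fixed testing order holds the family at 5%. Bonferroni over three contrasts uses 0.05 / 3 = 0.0167 each, giving 1 − (1 − 0.0167)³ = 0.049 if independent. At the implied SD of 15.1, 49 per group would then have 88.7% power, and 95% power would need 62 per group.

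**The case against.** The strongest reply is that this is a condensed article. Multiplicity rules usually sit in a full protocol or SAP, and a sentence defining significance at 5% is ordinary. It does not say that any significant test establishes efficacy. Moreover, 2.5 states only one hypothesis.

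Part of this stands. The lack of an adjustment method is not in itself an error, and reading any positive contrast as efficacy is a condition of the 12% figure, not something the article states. What the reply does not answer is that the elements the article does fix do not fit together: three conditions, a single-comparison 5%, and a hypothesis that neither separates A from B nor uses a trial outcome. The deciding contrast is more than a detail for later, because the sample size depends on it.

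Three stronger readings are tempting and are not supported:

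- **No hierarchy at all.** Section 2.4.1 does name the Vancouver scale as primary. The gap lies within that outcome.
- **Separate tests in each of eight weeks.** Scoring is weekly, but 2.7 sends repeated scores to repeated-measures ANOVA and MANOVA. Week-by-week tests are not stated, so error rates built on them do not apply.
- **Six independent chances.** The independent-test figure, 1 − 0.95⁶ = 0.265, ignores that the contrasts share conditions and that both measures use the same kind of formula.

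**Conclusion.** The point holds in limited form. The article sets one 5% threshold for every test, defines three conditions, and does not say which contrast or time point on its primary score decides efficacy. Its single hypothesis cannot fill that gap.

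The size is about 12% instead of 5%, provided all three pairwise contrasts are tested unadjusted and any positive one is taken as efficacy. This assumes two-sided tests and equal information for each contrast. The figure of about 20% with the four-class grade is softer, because it rests on an assumed link between the two measures. No exact error rate can be fixed, since the number of tests and their correlations are not stated. If the trial really makes one two-group comparison at one time point, the error on the primary score is 5%, but 2.3 would then have to change.

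**What to change.** 1. **Reconcile the design first.** Sections 2.5 and 2.6 describe two groups of patients; 2.3 describes three scars in each patient. The choice determines which contrasts can be interpreted.
2. **Name one deciding test in 2.7:** one contrast on the total scar score at week 8, two-sided alpha 0.05. State the hypothesis in 2.5 for the same contrast and scale. B versus A can be the deciding contrast only if patients are randomised between A and B. If all three scars are in the same patient, the oral decoction reaches all of them, and no claim about the decoction should rest on that contrast.
3. **Control the rest.** Test the remaining contrasts in a fixed order, each at 0.05 only if the previous one is significant, or use Holm across the three.
4. **Label** the four-class grade, single items and earlier weeks as secondary or exploratory, reported with estimates and confidence intervals.

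Steps 2 to 4 take a few sentences and a matching registry entry, and 2.9 says recruitment has not started. Step 1 is the larger task. A fixed order leaves the first test at the full 0.05, so the multiplicity rule itself adds no patients for that test. Whether 60 per group is enough cannot be judged, because 2.5 gives no SD and uses another scale. The cost is that results on the grade, single items or earlier weeks can no longer be claimed as confirmatory.
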